### Prospective longitudinal cohort study

The primary study will comprise a prospective longitudinal cohort study in which adults (n = 1300) with stage 3 CKD, enriched to include people more likely to have progressive kidney disease (i.e. those with proteinuria and/or diabetes), will be recruited from six UK centres. Participants will be recruited from both primary (two centres) and secondary/tertiary (four centres) care. People aged 18 years and older having stage 3 CKD (eGFR measurements between 30 and 59 mL/min/1.73 m^2^ inclusive sustained over at least 3 months prior to recruitment) will be included. Recruitment will be targeted such that 20% to 30% of recruits will have proteinuria (ACR ≥30 mg/mmol) and a similar proportion will have diabetes. The prevalence of proteinuria and diabetes will be monitored during the course of the study to ensure reasonable representation.

Participants will attend hospital in the morning having been advised to consume a light breakfast (no meat or fish). A clinical (including cardiovascular) and drug history will be recorded using a standardised questionnaire. Information on ethnicity will be gathered using a modified version of the 2011 UK Census Questionnaire. Height will be measured to the nearest 0.1 cm with a rigid stadiometer. Body weight will be measured in light indoor clothing to the nearest 0.1 kg. Waist circumference will be recorded to the nearest 0.1 cm at the mid-point between the lower costal margin and the level of the anterior superior iliac crest. Hip circumference will be measured at the widest point of the hips and the maximal protrusion of the gluteal muscles. Brachial blood pressure will be measured three times in the sitting position as recommended [56]. Blood will be taken for serum creatinine, cystatin C and a urine sample will be collected for ACR. Further aliquots of serum, plasma and urine will be stored for potential analysis of future markers of GFR. An iohexol reference GFR measurement will be undertaken in addition to estimation of GFR using four GFR estimating equations (MDRD, CKD-EPI_creatinine_, CKD-EPI_cystatin_, and CKD-EPI_cystatin-creatinine_) (Table 1).

Participants will be followed for three years. All the above measurements and the clinical questionnaire will be repeated at 36 months. At each 6 month interval, all participants will have blood taken for serum creatinine, cystatin C and a urine sample will be collected for ACR. GFR will be estimated as above.

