### Sub-study of patterns of disease progression

At three centres 125 each of Caucasian, African-Caribbean and Asian subjects (i.e. n = 375 in total), stratified in each group by higher and lower risk of disease progression (approximately 60 with diabetes and/or proteinuria and 60 with neither diabetes nor proteinuria) will undergo additional sampling every year over the 3 year study period. At each point indicated subjects will undergo a reference GFR measurement in addition to cystatin C and creatinine eGFRs and ACR. The study will enable a model of disease progression to be developed based on reference GFR measurement enabling optimal monitoring frequencies in a high-risk cohort to be defined. This number of subjects should provide a range of values over the main factors considered to influence disease progression and allow assessment of covariates in the statistical model. Further assessment of covariates will be performed by combining the data from this sub-study with the main study. Inclusions/exclusions and laboratory methods for this sub-study will be as above.

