#### Sub-study of patterns of disease progression

##### **How does GFR progress over time and what are the optimal monitoring times?**

The rate of decline (mL/min/1.73 m^2^/year) in reference GFR, and the difference between reference GFR and estimated GFRs (referred to as error), measured every 12 months will be modelled over time using a longitudinal linear or nonlinear (exponential decline) random coefficients regression model to estimate average and variability in disease progression and error. Parameters of the model for each outcome will be estimated using maximum likelihood. Covariates to be explored in the model will be as described above. The effect of covariates on the population average intercept and longitudinal time effect parameters will be assessed. The method of backward elimination will be used to remove covariates which are not significant from the model. A linear relationship between disease progression and drug name or drug class will be explored. Analysis will be undertaken using NONMEM version 7.1.2, R open source software and PFIM version 3.2.2 optimal design algorithms (R open source software). The PFIM algorithms will be used to calculate the D-optimal [62] sampling times from the disease progression model based on reference GFR for individuals with diabetes and/or proteinuria, and for those individuals with neither of these conditions. Optimal monitoring strategies will be selected from a set of designs and for important subgroups of the population found to be significant in the disease progression model. The monitoring strategies identified will be used as the basis for further simulations.

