#### Modelling monitoring strategies

Whilst our longitudinal cohort will not have adequate power to detect differences in progression, our estimates of the accuracy of eGFR (study 1), patterns and determinants of progression (study 2), and intra-individual biological variation (study 3) can be combined in a model to evaluate the impact of alternative monitoring strategies on detection of progression to stage 4 CKD. True GFR values will be modelled over time for representative cohorts of people, and performance of alternative monitoring strategies in detecting progression to stage 4 CKD (varying in timing and choice of eGFR equation) will be simulated utilising estimates of measurement error and accuracy. Outcome variables which will be assessed will include false positive progression rates, and the sensitivity and delays in detecting progression.

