We have chosen plasma iohexol clearance as the reference measure of GFR for our study because it is equivalent to inulin clearance, is widely used in clinical and research practice, is non-radioisotopic, can be measured accurately and precisely, and is cheap [13,65,66]. The CKD-EPI and MDRD equations will be studied because they are anchored to both creatinine and cystatin C reference methodology and therefore likely to generate data that will be valid in perpetuity. Other more recently published equations will also be evaluated (e.g. Berlin Initiative Study equations [28]). The study population will be a large cohort of people with stage 3 CKD including subjects of African-Caribbean and Asian ethnicity as well as subjects with diabetes and proteinuria. A sub-study will model disease progression in a smaller cohort. This will build on the findings of previous research, but using a prospective design with regular reference GFR measurements: the impact of medication on disease progression will be estimated and included in the model. The model will be used to define optimal sampling times for high and low risk participants, and other significant subgroups defined by the model. We will also use a classical study design to establish the biological variability of both reference and estimated GFR: this information will be used as one of the handles in defining progression and assessing the ability of GFR-estimating equations to detect it.

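### D-optimality on the reference-GFR model is the wrong rule for choosing monitoring strategies: over the 3-year follow-up it puts the samples at or near the two ends in both risk groups and yields no monitoring interval

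*Protocol article*

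**What the plan says.** Under Data analysis, the part on the sub-study of patterns of disease progression is headed by a question about optimal monitoring times. Reference GFR is to be modelled "using a longitudinal linear or nonlinear (exponential decline) random coefficients regression model". Then: "The PFIM algorithms will be used to calculate the D-optimal [62] sampling times from the disease progression model based on reference GFR", separately "for individuals with diabetes and/or proteinuria, and for those individuals with neither of these conditions". Strategies are to be picked from a set of designs that is not described, also for subgroups found significant in the model, and "The monitoring strategies identified will be used as the basis for further simulations".

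The Discussion repeats the purpose: "The model will be used to define optimal sampling times for high and low risk participants". The Methods section on the sub-study likewise says that the model will allow optimal monitoring frequencies to be defined in a high-risk cohort.

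Detection outcomes appear only in the later section Modelling monitoring strategies, which simulates strategies differing in timing and equation and reports "false positive progression rates, and the sensitivity and delays in detecting progression".

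**The concern.** A D-optimal design maximises the determinant of the information matrix for the model's parameters: mean baseline, mean decline and, if included, the variance components. It answers the question of when to sample a group so that the average trajectory is estimated precisely. Monitoring asks a different question: how often to test one patient so that progression is caught soon and with few false alarms. Nothing in the determinant rewards a short delay or a low false-alarm rate.

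For a straight line or a slow exponential, information about the decline is greatest at the ends of the window. The separate calculations for higher- and lower-risk people would then give much the same end-loaded design, reflecting the criterion and the window and not the clinical question. The designs are also computed on the error of the iohexol measurement, whereas patients would be monitored by eGFR. At stake is which strategies reach the simulation. Intervals of practical interest could be left out before any detection outcome is calculated.

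**Working it through.** The protocol gives no D-optimal times, so there is no figure to reproduce. The check applies its stated criterion to its stated model.

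**Inputs from the protocol**
- Window: 0 to 3 years ("Participants will be followed for three years").
- Reference measurements in the sub-study: 0, 1, 2 and 3 years, so four per person ("will undergo additional sampling every year over the 3 year study period").
- Baseline GFR: 30 to 59 mL/min/1.73 m².
- Decline (Background, Progression of kidney disease): 1.1 to 1.9 per year without diabetes, 2.8 to 3.6 with diabetes, 7.0 in proteinuric non-diabetic people.
- Residual variation: about 10%, with a reported range of 5.5% to 11.6%.

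**Assumed, because not stated:** between-person variability, and the 3-year follow-up as the design horizon.

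**Linear model, simplest case.** Ignoring random effects, with constant error, the determinant is proportional to n × Σ(t − mean t)².
- Annual times 0, 1, 2, 3: 4 × 5 = 20.
- Times 0, 0, 3, 3: 4 × 9 = 36.

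The decline rate does not enter, so risk group makes no difference.

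**Exponential model, constant error.** For f = b₀·exp(−kt) with one point at 0, the two-point determinant is proportional to t·exp(−kt), which is largest at t = 1/k. With k = decline ÷ baseline:

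| Decline per year | Baseline | k | 1/k (years) |
|---|---|---|---|
| 1.1 | 45 | 0.024 | 40.9 |
| 3.6 | 45 | 0.080 | 12.5 |
| 7.0 | 45 | 0.156 | 6.4 |
| 7.0 | 30 | 0.233 | 4.3 |

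All exceed 3 years, so the late point is pushed to the end of follow-up in every group.

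**Population information matrix with random effects.** This used a first-order approximation with exhaustive search.
- Four samples, baseline 45, declines 1.1, 3.6 and 7.0, both models, additive error 4.5 or proportional error 10%, assumed intercept SD 8 and slope CV 50% or 150%: 3 × 2 × 2 × 2 = 24 settings. With repeat samples allowed, every time was 0 or 3 years in all 24. With distinct 3-monthly times the optimum was 0, 3, 33, 36 months or 0, 3, 6, 36 months. The second pattern appears when the slope variance is large, or when error is proportional and decline is fast.
- A wider grid (baselines 30, 45 and 59, all five declines, residual CV 5.5%, 10% and 11.6%, assumed CV 15–30% on baseline and 50–150% on slope; 540 settings per sample number): all times at the ends in 1620 of 1620 with fixed effects only (2, 3 or 4 samples), and in 1080 of 1080 with variance components included (3 or 4 samples).

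**Where the pattern loosens**
- Two samples per person with variance components included: both ends in only 149 of 540.
- Seven distinct samples, linear model: clusters at 0–9 and 30–36 months, or 0–6 and 27–36 months, leaving a gap of 21 months.
- Assumed 10-year horizon, exponential model, decline 7.0 from 45, additive error: the late point moves to 7 years on a yearly grid (1/k = 6.4), still with only two distinct times.

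**Would a set of regular schedules rescue the criterion?** D-information relative to 12-monthly (baseline 45, proportional error 10%, declines 1.1 and 7.0) was 1.06–1.44 for 6-monthly, 0.83–0.97 for 18-monthly and 0.49–0.94 for 36-monthly. Per sample, multiply by 4/7 for 6-monthly, giving 0.61–0.82, and by 4/3 for 18-monthly, giving about 1.10–1.29. The total favours more samples. The per-sample value always puts 18-monthly above 12-monthly and 12-monthly above 6-monthly. Neither ranking measures detection.

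**The case against.** The strongest reply is that the right evaluation is already planned. Modelling monitoring strategies simulates eGFR strategies that differ in timing, uses estimates of measurement error and accuracy, and reports false positives, sensitivity and delay. This stands. The mismatch between iohexol error and eGFR error therefore touches only the upstream selection step.

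The candidate set, number of samples, minimum spacing and horizon are also unstated, and a condensed article may leave them to a fuller document. This stands too. A reader might infer that the simulations will test only strategies with visits at 0 and 3 years and nothing between. The text does not say so: being a basis for simulations does not exclude other timings, and seven distinct samples would not be purely end-point designs. Nor can one say that risk groups are never separated, since on a 10-year horizon the late point differs for fast exponential decline with additive error.

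A reader might also infer that the cost-effectiveness result is compromised. The Health economics study compares cystatin C-based or combined eGFR with MDRD, not one interval with another, and no dependence on D-optimal times is shown.

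What the reply does not remove is that the criterion itself is stated, is the only one given, and does not match the question it is meant to answer. Supplying a horizon or a candidate set would not change that.

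**Conclusion.** The point holds for the selection step. D-optimality on the reference-GFR model cannot supply a monitoring interval. Over the 3-year follow-up, with the sub-study's four measurements and the protocol's decline rates, it places samples at or near the two ends in higher- and lower-risk people alike. The split between the ends depends on the assumed slope variance, and the result also rests on taking follow-up as the design horizon. For three or four samples with repeats allowed, the end-point result did not depend on the variability assumed within the ranges tried. A longer horizon can shift the late point but leaves a two-point design.

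The consequence is limited to which strategies enter the simulations. The P30 and large-error comparisons are untouched, and an effect on cost-effectiveness is not shown. It is worth correcting because it decides what gets tested.

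**What to change.** Do not use D-optimality to select monitoring strategies. State in the analysis plan that the simulations under Modelling monitoring strategies will cover a pre-specified grid of regular eGFR intervals, including the study's 6-monthly and annual schedules. Simulate from the fitted progression model with eGFR error, and rank the intervals, by equation and risk group, on false-positive progression rate, sensitivity and delay to detection. State the simulation horizon. Keep PFIM only to describe how precisely the progression model's parameters are estimated, and align the sub-study and Discussion sentences that promise optimal times from the model.

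The cost is analysis-plan wording. The simulation is already planned, PFIM loses its selecting role, and no visit, sample or data item changes.

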#### Study of intra-individual biological variation

Pre-analytical variables will be standardised as described above. All samples for all analytes will be assayed in duplicate and the analytical variance (SD_A_^2^) will be calculated from the differences between the duplicate measurements. The total (CV_T_), analytical (CV_A_) and within-individual (CV_I_) components of variation will be calculated using nested ANOVA [19]. The critical difference (reference change value, RCV) for significant changes in serial results (P less than 0.05) and the number of specimens required to estimate the homeostatic set-point of an individual (within ±10% with a confidence of 95%) will also be estimated. The derived RCV for the reference GFR will be used to test the ability of estimated GFR equations to detect a true change in GFR (see study 1, part 2 above).

#### Modelling monitoring strategies

Whilst our longitudinal cohort will not have adequate power to detect differences in progression, our estimates of the accuracy of eGFR (study 1), patterns and determinants of progression (study 2), and intra-individual biological variation (study 3) can be combined in a model to evaluate the impact of alternative monitoring strategies on detection of progression to stage 4 CKD. True GFR values will be modelled over time for representative cohorts of people, and performance of alternative monitoring strategies in detecting progression to stage 4 CKD (varying in timing and choice of eGFR equation) will be simulated utilising estimates of measurement error and accuracy. Outcome variables which will be assessed will include false positive progression rates, and the sensitivity and delays in detecting progression.

#### Health economics study

The aim of the health economics evaluation is to determine the cost-effectiveness of implementing cystatin C-based eGFR or a combination of both cystatin C and creatinine-based eGFR in subjects that are initially stage 3 CKD compared with MDRD (creatinine-based) eGFR alone. The cost-effectiveness analysis will take the form of a cost-utility analysis in which the outcome measure will be the cost per quality adjusted life year (QALY). This will be undertaken by extending the monitoring strategy by extrapolating the rate of change in GFR beyond the end of the trial through the use of secondary data sources to link the error in estimated GFR to patient outcomes, which will include myocardial infarction, kidney transplant, and established renal failure. It is unlikely that differences in quality of life will be seen for patients receiving alternative monitoring strategies during the period of the trial, and therefore quality of life data (e.g. EQ-5D) is not being collected during this study. Instead secondary sources will be used to inform the impact of the long term outcomes of CKD on quality of life.

Cost data collection will be undertaken prospectively for all subjects in the cohort study in order to inform the cost component of the cost-effectiveness analysis. The main resource uses monitored during the trial will include the following:

1. Diagnostic testing procedures implemented.

2. Resource uses involved in the diagnostic testing procedures (e.g. urine ACR).

3. Other related procedures, including level of health care professional involvement in the procedure, equipment required, overheads, consumables etc.

The costs obtained will be dictated by the recommended investigations and interventions by GFR category in NICE Clinical Guideline 73 [6]. The difference in cost will be that between GFR category and rate of change in GFR assessed by creatinine-based estimating equations versus cystatin C-based equations.

The model-based analysis will be carried out following the conclusion of the data collection undertaken during the cohort study. A decision analytic model will be used to allow extrapolation of the cost and effectiveness parameters beyond the data observed during the trial (and to allow extrapolation to other settings). The model will consider the impact of the error in GFR measures on patient outcomes. The results of the economic analysis will be presented using cost-effectiveness acceptability curves to reflect sampling variation and uncertainties in the appropriate threshold value by which the cost-effectiveness of the different diagnostic strategies will be judged.

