**Methods/design:**

Iohexol measured GFR will be the reference against which each estimating equation will be compared. The estimating equations will be based upon serum creatinine and/or cystatin C. The eGFR-C study has 5 components:

1) A prospective longitudinal cohort study of 1300 adults with stage 3 chronic kidney disease followed for 3 years with reference (measured) GFR and test (estimated GFR [eGFR] and urinary albumin-to-creatinine ratio) measurements at baseline and 3 years. Test measurements will also be undertaken every 6 months. The study population will include a representative sample of South-Asians and African-Caribbeans. People with diabetes and proteinuria (ACR ≥30 mg/mmol) will comprise 20-30% of the study cohort.

2) A sub-study of patterns of disease progression of 375 people (125 each of Caucasian, Asian and African-Caribbean origin; in each case containing subjects at high and low risk of renal progression). Additional reference GFR measurements will be undertaken after 1 and 2 years to enable a model of disease progression and error to be built.

3) A biological variability study to establish reference change values for reference and test measures.

4) A modelling study of the performance of monitoring strategies on detecting progression, utilising estimates of accuracy, patterns of disease progression and estimates of measurement error from studies 1), 2) and 3).

5) A comprehensive cost database for each diagnostic approach will be developed to enable cost-effectiveness modelling of the optimal strategy.

The performance of the estimating equations will be evaluated by assessing bias, precision and accuracy. Data will be modelled as a linear function of time utilising all available (maximum 7) time points compared with the difference between baseline and final reference values. The percentage of participants demonstrating large error with the respective estimating equations will be compared. Predictive value of GFR estimates and albumin-to-creatinine ratio will be compared amongst subjects that do or do not show progressive kidney function decline.

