### Estimating GFR

Use of the MDRD Study equation (MDRD) [9,20,21], which estimates GFR adjusted for body surface area (BSA), has been endorsed by national professional healthcare organisations [6,22]. However, accuracy of the equation is sub-optimal. In the CKD field, accuracy of GFR estimating equations is commonly expressed as the P_30_, the percentage of eGFR values within 30% of ‘true’ GFR. This metric captures aspects of both imprecision (measurement error) and bias (systematic over- and/or under-estimation). Reported P_30_ values for the MDRD equation typically range between 73% to 93% [23]. The MDRD equation has also been criticised on the basis that it significantly underestimates GFR (particularly in individuals with GFR greater than 60 mL/min/1.73 m^2^) and has poor precision [10].

A revised equation, the Chronic Kidney Disease Epidemiology Collaboration (CKD-EPI_creatinine_) produces less biased estimates of GFR at higher levels of kidney function [10], although reportedly less accurate estimates as GFR falls below 60 mL/min/1.73 m^2^[23]. P_30_ values for the CKD-EPI_creatinine_ equation are slightly superior to those of the MDRD equation in studies that have undertaken a head-to-head comparison [23]. Cystatin C has been proposed as an improved marker of GFR compared with creatinine [24,25]. Recently, the CKD-EPI Collaboration have published two further CKD-EPI equations; one based on cystatin C (CKD-EPI_cystatin C_) and one using both cystatin C and creatinine (CKD-EPI_cystatin and creatinine C_) [26]. In the external validation datasets of Inker et al. [26] the CKD-EPI_cystatin C_ and CKD-EPI_cystatin and creatinine C_ equations achieved P_30_ values of 86% and 92% respectively. There has been little independent validation to date of these latter equations [27,28]. Amongst older people the MDRD equation achieved a P_30_ of 81% compared with 86% for the CKD-EPI_cystatin and creatinine C_ equation [27].

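### The stated economic aim sets the cystatin C strategies against MDRD alone and does not name CKD-EPI creatinine, so it cannot separate a change of marker from a change of equation

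*Protocol article*

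**What the plan says.** The Health economics study section names two strategies to be evaluated: "implementing cystatin C-based eGFR or a combination of both cystatin C and creatinine-based eGFR". A single creatinine equation serves as the comparator, since the evaluation is to be made "in subjects that are initially stage 3 CKD compared with MDRD (creatinine-based) eGFR alone". CKD-EPI creatinine appears there neither as a strategy nor as a comparator.

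The cohort itself covers more. Under Prospective longitudinal cohort study, GFR is estimated with "four GFR estimating equations (MDRD, CKD-EPI_creatinine_, CKD-EPI_cystatin_, and CKD-EPI_cystatin-creatinine", at baseline and at each six-monthly visit.

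Three other places are worded more broadly than the aim:
- Later in the Health economics section, the cost difference is described as depending on "rate of change in GFR assessed by creatinine-based estimating equations versus cystatin C-based equations", with creatinine equations in the plural and none named.
- The monitoring model, which the economic analysis extends, compares strategies "varying in timing and choice of eGFR equation".
- The abstract says: "A comprehensive cost database for each diagnostic approach will be developed to enable cost-effectiveness modelling of the optimal strategy".

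**The concern.** The decision at stake is whether the health service should pay for cystatin C, which the Background and Discussion describe as considerably dearer than creatinine. A laboratory that does not buy the assay has two creatinine options in this study, not one: stay with MDRD, or apply CKD-EPI creatinine to the same result. The aim names only the first.

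Both cystatin equations in the study belong to the CKD-EPI family. Setting them against MDRD changes the marker and the equation family in one step. Any gain or loss that comes from the family would be attributed to the assay. If part of the gain could be had without the assay, its cost per QALY would look better than it is.

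**Working it through.** No sample size, power or other stated figure depends on this point, so there is nothing to reproduce. The check has three steps.

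**1. Does CKD-EPI creatinine need anything extra?** In Table 1 both creatinine equations take serum creatinine, age, sex and black ethnicity. The difference lies in coefficients and functional form. No additional assay is needed, and the values are already calculated for all participants.

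**2. Which way can the omission move the adoption result?** At a given threshold, write NB(M), NB(K) and NB(C) for the net benefit of MDRD, CKD-EPI creatinine and a cystatin strategy.
- Incremental net benefit under the stated aim: NB(C) − NB(M).
- Incremental net benefit against the better creatinine option: NB(C) − max{NB(M), NB(K)}.
- Since max{NB(M), NB(K)} ≥ NB(M), the second can never exceed the first.

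If NB(K) ≤ NB(M), the two are equal and CKD-EPI creatinine drops out. If NB(K) > NB(M), the stated aim is too favourable to cystatin C by NB(K) − NB(M). This holds even if downstream costs differ by equation, because costs are inside NB. The same applies to the acceptability curves: adding a strategy cannot raise the probability that a cystatin strategy is optimal.

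**3. Do the documents say whether NB(K) exceeds NB(M)?** They do not. The Estimating GFR section says P30 "values for the CKD-EPI_creatinine_ equation are slightly superior to those of the MDRD equation in studies that have undertaken a head-to-head comparison", but gives no figure. The same paragraph reports that the equation becomes less accurate below 60 mL/min/1.73 m². Participants enter with eGFR 30 to 59, so that caveat covers the study's own range.

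To show how open this is, take the one MDRD-versus-combined contrast in that section: P30 of 81% for MDRD and 86% for the combined equation in older people, a gap of 5 points. The gap splits as (K − 81) from the equation plus (86 − K) from the assay, where K is the P30 of CKD-EPI creatinine. K is an assumption.

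| Assumed K (%) | From equation (points) | From assay (points) | Equation share of gap |
|---|---|---|---|
| 79 | −2 | 7 | −40% |
| 80 | −1 | 6 | −20% |
| 81 | 0 | 5 | 0% |
| 82 | +1 | 4 | 20% |
| 83 | +2 | 3 | 40% |
| 84 | +3 | 2 | 60% |

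Attribution to the marker can therefore err in either direction. The adoption result in step 2 can err in only one. P30 is not net benefit, so the table shows only that the sign is undetermined. It does not estimate an economic effect.

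**The case against.** **MDRD is a proper reference.** The article says that national bodies support its use, the costs follow the national guideline, and the sample size rests on MDRD against CKD-EPI cystatin C. Comparing a new test with current practice is a legitimate question. This stands as a reason to keep MDRD in the model. It does not justify making it the only creatinine strategy when a second is already calculated.

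**The article does not exclude CKD-EPI creatinine.** A reader might infer from the aim that the equation has been ruled out of the economic work. The documents do not support that. The plural creatinine equations in the cost contrast, the varying choice of equation in the monitoring model and the cost database for every approach all leave room for it. What stands is that the aim is narrower than this text, and the two need to agree.

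**A condensed article may leave the list of strategies to a fuller plan.** That would answer a complaint that the list is missing. Here the article states a comparator, and the point concerns that statement.

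**The direction of any bias is not established.** This is correct. A reader might infer that the plan does overstate the value of cystatin C. That would need CKD-EPI creatinine to be the better creatinine option in stage 3 CKD, and the article's own evidence is mixed.

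**Conclusion.** The point holds in a limited form. As stated, the economic aim compares the cystatin strategies with MDRD alone, leaves CKD-EPI creatinine unnamed, and so mixes a change of equation family with a change of marker. For the adoption decision, the omission either makes no difference or makes cystatin C look too favourable. Which of these applies depends on whether CKD-EPI creatinine has higher net benefit than MDRD in this population.

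The size cannot be derived from the documents. A reader might be tempted to assume that a share f of the effect is available without the assay and to multiply the cost per QALY by 1/(1 − f). Nothing in the article supports a value of f, which could be zero or negative. The formula also holds incremental cost fixed, whereas the plan ties cost to GFR category and rate of change, both of which may shift with the equation.

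The conclusion rests on two assumptions: that the aim sentence defines the strategies to be modelled, and that switching between creatinine equations needs no extra test. Table 1 supports the second. The article does not cost any other aspect of switching.

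**What to change.** - Restate the aim in the Health economics study section so that MDRD, CKD-EPI creatinine, CKD-EPI cystatin C and the combined equation are all strategies in the decision model, with MDRD identified as current practice.
- Report a full incremental analysis: order the strategies by cost, remove dominated ones, and compare the cystatin strategies with the best non-dominated creatinine equation. The contrast with MDRD can be shown alongside.
- Draw the acceptability curves over all four strategies.
- Bring the aim into line with the broader wording in the abstract, the Modelling monitoring strategies section and the cost contrast in the Health economics section.

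The cost is one further strategy in the model and a slightly longer results table. The equation is already calculated for every participant, so no new tests, visits or participants are needed.
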